# **5. Subject selection policy**

## 5.1. Selection criteria

Patients who meet all of the following

At the time of temporary registration

- 1. Patients diagnosed with chronic constipation according to the Rome IV criteria for the diagnosis of chronic constipation
  2. Age: 20 years or older (at the time of obtaining consent)
  3. Gender: Any
  4. Outpatients
  5. Patients for whom written consent can be obtained
  6. Patients who can record defecation, etc. in the patient diary

　　At the time of registration: Dosing start criteria

Patients with the following

Patients with loss of defecation desire* in the second week of the observation period (1 week before the start of the treatment period)

*"Loss of defecation desire " refers to patients whose "presence or absence of defecation desire " on the patient questionnaire was "4. almost never, 5. never".

(Basis for setting: At the time of temporary registration)

1. We have used the internationally widely used Rome IV as the diagnostic criteria for chronic constipation.
2. To participate in the study of their own free will, participants had to be at least 20 years of age to legally give their personal consent.
3. Set in order to maximize the number of patients we will be able to recruit.

(4) Constipation is mainly treated as an outpatient condition.

1. Set in compliance with the spirit of the Declaration of Helsinki.
2. Set in order to properly evaluate the efficacy of study drugs.

　　(Basis for setting: At the time of registration)

　　The primary endpoint of 　　the study was set to be assessed correctly.

## 5.2. Exclusion criteria

Patients who meet any of the following conditions should be excluded

At the time of temporary registration

1. Patients with organic constipation or suspected of having organic constipation
2. Patients with or suspected of having functional ileus
3. Patients with or suspected of having inguinal hernia
4. Patients with a history of open abdominal surgery within 12 weeks prior to obtaining consent (excluding appendicitis resection)
5. Patients with a history of surgical or endoscopic procedures related to gallbladder resection and papillotomy
6. Patients with complications of malignancy

However, patients who have undergone radical surgery or who have completed chemotherapy or radiotherapy may be registered.

1. Pregnant women, lactating women, women who may be currently pregnant, or women who use contraception while participating in the study.

Patients who do not give their consent to be

1. Patients with serious renal, hepatic, or cardiac disease
2. Patients with a history of drug allergy to this study drug
3. Patients who are participating in other clinical research, or who participated in other clinical research within 4 weeks before obtaining consent

Patients who participated in the study but not in observational studies

1. (3) Any other information that the principal investigator or sub-investigator deems inappropriate for conducting this research.

disabled patient

At the time of registration: Dosing start criteria

(1) Patients whose doses of concomitantly restricted medications were increased during the observation period

(2) Patients who used concomitantly prohibited drugs during the observation period

(Basis for setting: At the time of temporary registration)

- 1. ~5) Set because they may affect the efficacy of the study drug.

(6) to (9) were set to ensure the safety of the subjects.

(⑩) Set to eliminate any effects on ethical considerations and the evaluation of study drugs.

(⑪) In addition to the above, it is judged that the subject of this research is inappropriate from the scientific aspect, ethical viewpoint, etc.

It was set assuming the case where the data is used for the first time.

(Basis for setting: At the time of registration)

　　　　　　　　(1) (2) The primary endpoint of this study was set to be evaluated correctly.

# **6. Research plan**

## 6.1 Research Design

A multicenter, single-arm, open-label, before-and-after study

## 6.2. Target number of cases

　　40 cases (as the number of registered cases)

## 6.3. Research period

Registration period: from the date of jRCT publication (date of notification by the Minister of Health, Labour and Welfare) to July 31, 2022

Study period: From the date of publication of the jRCT (date of notification to the Minister of Health, Labour and Welfare) to March 31, 2023 (approximately 2 years)

Planned duration of subject participation: up to 9 weeks from obtaining consent

Observation period: 2~4 weeks

Treatment period: 4 weeks (maximum 5 weeks)

## 6.4 Facility Registration and Case Registration

Institutional registration shall be done by central registration at the data center.

Case registration will be possible from the implementing medical institution that has completed the facility registration.

6.4.2. Facility registration

The principal investigator of each medical institution shall obtain approval for the implementation of the study from the administrator of the medical institution after approval by the accredited clinical research review committee, and then send a copy of the administrator's approval letter to the data center. The data center shall register the facility and notify the principal investigator by sending a notice of completion of facility registration.

6.4.3 Enrollment of Subjects

　 The principal investigator or sub-investigator assigns a subject identification code for all subjects who have given consent. The eligibility test will be conducted, and at the time of provisional registration, registration-related information will be entered into the eCRF: Registration Form and saved. If a subject is judged to be "eligible", a case registration number will be displayed on the EDC system screen. The case registration number is recorded in the subject screening list.

At the time of registration, confirm that the patient meets the criteria for starting treatment, and enter and save the registration-related information in the eCRF: Registration Form. If the case is determined to be "Full Registration", the word "Full Registration" will be displayed on the EDC system screen. Prescribe the study medication to the enrolled subjects. Record the date of "Full Registration" in the Subject Screening List. For cases that do not meet the dosing start criteria, enter and save the pre-start dropout information on the eCRF: Full Registration form.

　　Subjects who do not meet the criteria for starting dosing and who drop out before starting dosing may be re-enrolled. In this case, consent should be obtained again from the subject, and eligibility tests should be conducted and confirmed.

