**7. Observation, examination, investigation and evaluation items**

## 7.1 Schedule

|  | Obtaining  consent | Observational periods | | Treatment periods |
| --- | --- | --- | --- | --- |
|  |  | V1 | V2 | V3/EOT |
| Week |  | Provisional registration | Before treatment/final registration | 4 weeks |
| Allowance |  | － | After provisional registration 2~4 weeks | ±7日 |
| Obtaining consent | ○ |  |  |  |
| Selection/exclusion criteria |  | ○ | 〇 |  |
| Subject background |  | ○ |  |  |
| Vital sign ^a^ |  |  | ○ | ○ |
| Subjective/objective symptoms findings |  |  | ○ | ○ |
| hematological tests |  |  | 〇 | ○ |
| Biochemical tests |  |  | 〇 | ○ |
| Provisional registration |  | ○ |  |  |
| Final registration/ Dosing start criteria |  |  | ◎ |  |
| Blood and stool for exploratory research samples* collection |  |  | ● | ● |
| Research drug prescription |  |  | ○ |  |
| Checking medication status |  |  |  | ○ |
| Investigation of concomitant medications |  | ○ | ○ | ○ |
| Investigation of adverse events |  |  |  |  |
| Patient Diary ^b^ |  |  |  |  |
| Patient Questionnaire^c^ |  |  | 〇 |  |
| questionnaire survey ^d^ |  |  | 〇 | 〇 |

*: Provide stool collection kits for V1 and V2.

a: Blood pressure Pulse

b: Provide patient diary (for observation period) to V1, check and collect from V2.

　 Provide patient diary (for therapeutic phase) to V2, check and collect to V3.

^c^： V2 Patient questionnaire will be administered on arrival at the hospital.

Patient questionnaires for the treatment period are provided to V2, and checked and collected by V3.

^d^: JPAC-QOL and constipation score (CSS) will be conducted at V2 and V3 visits.

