16.2 Basis for setting the target number of cases

The target number of patients is 40 cases for this registration.

[Basis for setting]

　　There are no studies investigating the recovery of defecation desire by treating chronic constipation. According to a WEB survey [4] of 2098 Japanese patients conducted at Yokohama City University, the rate of loss of defecation desire (no defecation desire: none + almost none) before treatment for Rome IV chronic constipation and in healthy adults was 57.4% (no defecation desire: none + almost none). 1484/2587 cases) and 8.3% (214/2587 cases), and the rate of defecation desire disappearance in outpatient treatment cases was 27.1% (120/443 cases).

Since the subjects of this study were "patients without defecation desire " who had already been treated for chronic constipation within the scope of usual care, the expected improvement rate of loss of defecation desire was assumed to be 45%, which was lower than 62.1%. The threshold rate of spontaneous change in defecation desire was assumed to be 20%. If the threshold is 20%, the expected value is 45%, the one-sided α is 0.025, and the total number of cases is 37, the power is calculated to be 91.6%, which is statistically significant if the number of cases is 13 or more out of 37. Although within the scope of normal practice, we considered that some patients may drop out of the study after provisional enrollment, so we judged that 40 cases was an appropriate target number of patients for this study.

The number of patients with chronic constipation who were expected to meet the eligibility criteria, including "no defecation desire," at each institution was examined, and it was determined that the number of patients could be accumulated without problems within the study period (the planned enrollment period of approximately six months).

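### Re-enrolment after a failed desire score is unrestricted and can bias the primary improvement rate upward; the size is not derivable from the protocol

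*Protocol*

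**What the plan says.** Section 6.4.3 of the protocol deals with subjects who fail at final registration: "Subjects who do not meet the criteria for starting dosing and who drop out before starting dosing may be re-enrolled". The only conditions follow directly: "In this case, consent should be obtained again from the subject, and eligibility tests should be conducted and confirmed". No reason for failure is excluded, and neither a maximum number of attempts nor a minimum interval is given.

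There are three dosing-start criteria. One is an inclusion criterion (section 5.1): "Patients with loss of defecation desire* in the second week of the observation period", defined as answer 4 or 5 on the desire item of the patient questionnaire. The other two are exclusions (section 5.2): a dose increase of a restricted concomitant drug, or use of a prohibited one, during observation. The footnotes to the schedule in section 7.1 show that the qualifying score is a single reading: "V2 Patient questionnaire will be administered on arrival at the hospital".

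Section 16.3.1.1 counts as improved a subject outside the two lowest desire categories at treatment week 4, that is, a score of 1-3 on the same item. The proportion is tested by a one-sided exact binomial test at 2.5% against 20%. Section 16.2 gives the origin of that figure only as an assumption: "The threshold rate of spontaneous change in defecation desire was assumed to be 20" percent. The same section says that no study has examined recovery of defecation desire under treatment.

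**The concern.** The entry criterion and the endpoint are mirror images on one five-point item. A subject turned away for scoring 1-3 has already been, off study drug, in the state that will later be counted as success. If the subject is re-enrolled and scores 4 or 5 on one later reading, a return to the usual level by week 4 is counted as improvement.

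In a randomised trial the control arm would share this drift. Here the comparator is a constant. Any selection that raises the untreated improvement rate of the enrolled group goes straight into the observed proportion and uses up the margin over 20% on which the only confirmatory test depends.

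**Working it through.** **1. The plan's own figures.** Inputs from section 16.2: n = 37, threshold 20%, expected 45%, one-sided alpha 0.025, critical value 13. Exact binomial:
- P(X ≥ 13 | 37, 0.20) = 0.0231 and P(X ≥ 12 | 37, 0.20) = 0.0517, so 13 is the smallest valid critical value.
- P(X ≥ 13 | 37, 0.45) = 0.916. The stated 91.6% reproduces.
- With all 40 enrolled subjects analysed, 14 successes are needed: P(X ≥ 14 | 40, 0.20) = 0.0194, with power 0.925.

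**2. How thin the margin is.** P(X ≥ 14 | 40, p) for an untreated improvement rate p:

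| p | 20% | 21% | 23% | 25% | 30% |
|---|---|---|---|---|---|
| P | 1.9% | 2.9% | 5.8% | 10.3% | 29.7% |

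**3. Direction.** Assume that subjects differ in their usual level, that readings vary around it, and that there is no true deterioration between screens. A reading of 1-3 at one screen is then evidence of a better usual level, so the chance of 1-3 at week 4 is higher than for a subject who qualified at the first screen. Over 15 combinations (prevalence of loss 50-75%, correlation between occasions 0.5-0.9), re-screened qualifiers had untreated rates of 36-50%, against 8-33% for first-time qualifiers.

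**4. Size, under assumptions.** The protocol gives neither the number of re-enrolments nor the week-to-week variability of the item. Assume a latent-normal score with prevalence π of loss at any screen and correlation ρ between occasions, an inert drug, and every desire-score failure re-screened once. Write L for loss (4-5) and N for no loss (1-3).
- First-time qualifiers: p1 = P(L,N)/π.
- Re-screened qualifiers: p2 = P(N,L,N)/P(N,L).
- Blended rate: [P(L,N) + P(N,L,N)] / [π + P(N,L)].

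For π = 50%, ρ = 0.8 this can be done by hand:
- P(L,N) = 1/4 − arcsin(0.8)/(2π), with π here the circle constant, = 0.25 − 0.1476 = 0.1024.
- p1 = 0.1024/0.5 = 20.5%. By symmetry p2 = 50%.
- Share re-screened = 0.1024/0.6024 = 17%.
- Blended rate = (0.1024 + 0.0512)/0.6024 = 25.5%.

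The other rows are by numerical integration; simulation agrees to within about 0.2 percentage points.

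| π | ρ | p1 | Blended | P(≥14/40), no re-enrolment | P(≥14/40), all failures re-screened once |
|---|---|---|---|---|---|
| 50% | 0.8 | 20.5% | 25.5% | 2.4% | 11.8% |
| 57.4% | 0.8 | 17.5% | 22.0% | 0.6% | 4.2% (4.3% simulated) |
| 50% | 0.9 | 14.4% | 18.8% | 0.1% | 1.2% (1.1% simulated) |
| 70% | 0.8 | 12.7% | 16.2% | <0.1% | 0.3% |
| 50% | 0.7 | 25.3% | 30.3% | 11.2% | 31.2% |

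The 57.4% is the pre-treatment loss rate from the web survey cited in section 16.2; the other values of π and ρ are assumptions. If only half of the failures are re-screened in the 57.4% row, the blended rate is 20.0% and the error about 1.9%.

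**5. A simpler cross-check.** Fix first-time qualifiers at 20% and re-enrolled subjects at an assumed 50%. Shares of 10%, 20% and 30% give blended rates of 0.2(1 − f) + 0.5f = 23%, 26% and 29%, and P(≥14/40) of 5.8%, 13.3% and 25.0%. With 10% re-enrolled at an assumed 30%, the rate is 21% and the error 2.9%.

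**The case against.** Re-screening is a common and legitimate design feature, and no other section contradicts it. A re-enrolled subject must still show loss in the week before dosing and so belongs to the stated target population. The 20% threshold is meant to cover spontaneous change. Each attempt needs new consent and a further 2-4 week observation period, within an enrolment period that section 16.2 puts at about six months. That section also says that sites counted candidates expected to have no defecation desire, which points to few failures. A subject whose condition truly worsened between screens does not fit the drift argument. The case report form records pre-start dropouts, and a sensitivity analysis could be placed in a statistical analysis plan that is not shown.

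Much of this stands as to size. It does not alter the direction, and no section shows that the 20% was chosen with re-enrolled desire-score failures in mind.

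Two stronger readings are tempting. A reader might infer that subjects are to be screened repeatedly until they score 4 or 5. The text only permits re-enrolment, and repeated attempts are inferred from the missing cap. A reader might also infer that the 2.5% error rate is lost as a matter of course. The table shows otherwise: with every failure re-screened, the error is still 1.2% at correlation 0.9 and 0.3% at prevalence 70%. In the opposite direction, at prevalence 50% and correlation 0.7 it is already about 11% with no re-enrolment. There the single baseline reading and the unsourced threshold are the main problem.

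**Conclusion.** Unrestricted re-enrolment after a desire-score failure is an avoidable source of upward bias in the primary improvement rate. The direction follows from the text, given stable differences between subjects and no true worsening between screens. The magnitude cannot be derived from the protocol. With every failure re-screened once, the false-positive probability at 14/40 is about 12%, 4%, 1% or 0.3% in the first four scenarios above. Among all the scenarios tabulated, it exceeds 2.5% only where first-time qualifiers already improve untreated at a rate within a few points of 20% (17.5% and 20.5%) or above it (25.3%). Restricting re-enrolment removes only the added part; regression to the mean from the single V2 reading remains. This should be fixed, with moderate confidence about how much it matters in practice.

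**What to change.** In section 6.4.3, limit re-enrolment to subjects who failed only dosing-start exclusion (1) or (2) in section 5.2, the concomitant-drug criteria, and state that a subject with a V2 desire score of 1-3 may not be re-enrolled. If any such subjects have already been re-enrolled, link their registrations, flag them, and repeat the primary analysis without them as a sensitivity analysis.

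The sample size, critical value and power are unchanged (13 of 37 with 91.6%; 14 of 40 with 92.5%), and no assessment is added. The cost is one sentence and slightly slower recruitment.

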6.4.4 Allocation Method and Allocation Adjustment Factors

　　Not applicable.

6.4.5 Method of blinding

　Not applicable.

6.4.6 Determining the need for and procedures for opening emergency key codes

　　　Not applicable.

6.4.7 Opening the Study drug Allocation Code Table

Not applicable.

## 6.5. treatment plan

6.5.1. protocol treatment

Description.

consent acquisition

Observation period: 2~4 weeks

Patient diary entry

Confirmation of dosing criteria

Eligibility check

Provisional registration

Treatment period 4 weeks

Writing patient diary/patient questionnaire

Observation period

Treatment period

final registration

6.5.1.1. observation period

Observation period: 2~4 weeks

The subject will keep a patient diary during the observation period.

6.5.1.2. treatment period

After the end of the observation period, administration of the study drug will be started on the day of enrollment after confirming that the patient meets the criteria for starting the drug. Patient diary entries and questionnaires should be completed throughout the treatment period.

Elobixibat is administered orally once daily before meals for 4 weeks.

The starting dose of elobixibat is 10 mg (2 tablets), and the dose can be increased or decreased (5 mg: 1 tablet or 15 mg: 3 tablets) according to the symptoms.

[figure not shown]

6.5.2. Concomitant medications/adjunct therapy

6.5.2.1 Restricted Concomitant Drugs and Therapies: Observation Period to End of Treatment Period (Final Dose)

Chronic constipation medications (including over-the-counter medications, supplements, etc.) and therapies used prior to enrollment should not be changed in principle until the end of the treatment period. However, dose reduction or discontinuation is acceptable. The use of enemas, suppositories, and stool extraction is permitted only when adequate defecation is not observed.

6.5.2.2 Concomitant medications prohibited: from observation period to end of treatment period (last dose)

The use of the following drugs, which may affect this study, is prohibited.

Bile acid transporter inhibitors other than study drugs

Bile acid preparations (ursodeoxycholic acid, kenodeoxycholic acid, dehydrocholic acid)

Antacids containing aluminum (sucralfate hydrate, aldioxa, etc.)

Cholestyramine, Cholestymid

6.5.2.3 Concomitant medications: during treatment (until last dose)

Drugs that should be used with caution are listed below.

-Digoxin

Dabigatran etexilate methanesulfonate

Midazolam

6.5.3. Instruction of subjects

At the time of provisional enrollment, the principal investigator or sub-investigator will hand out the patient diary to the subjects and instruct them on how to write it and the following precautions. For patients who have been enrolled in the study, the patient diary and patient questionnaire will be filled out, the method of taking the study medication will be explained, and the following precautions will be explained again.

1. Patients should not change their lifestyles, such as diet and exercise, during the study period.
2. Instruct the patient to complete the patient questionnaire provided at the time of this registration on a weekly basis.
3. Patients should be instructed to keep a patient diary from the beginning of the observation period to the end of the study medication, and to record the status of defecation, the status of taking the study medication, and the status of using suppositories and enemas.
4. When visiting another hospital, patients should inform the physician of your participation in the study. They should inform the principal investigator or sub-investigator in advance of the visit to another hospital and of any new prescription medications, tests, or treatments.
5. Patients must come to the hospital on the prescribed day, and if they cannot come to the hospital due to unavoidable circumstances, you must contact the hospital in advance.
6. Patients should tell the principal investigator or sub-investigator about any medications, supplements, or treatments you are taking, including prescription medications from other hospitals or over-the-counter medications purchased at pharmacies.
7. The study drug should be taken before meals once a day from the day of administration according to the instructions of the principal investigator or sub-investigator.
8. If patients miss a dose, take it on the same day if possible.
9. Be sure to bring the remaining medication, patient diary, and patient questionnaire to the next visit.
10. Bring the stool samples collected at the time of visit (V2 , V3).
11. When you come to the hospital (V2, V3), you should fast from 8 hours before the test because the blood test will be performed.
12. Women of childbearing potential should use an appropriate method of contraception from the time of obtaining consent until the end of the treatment period.

6.5.4. Dose reduction and withdrawal criteria

not applicable

6.5.5. Criteria for volume increase and resumption

　　not applicable

**7. Observation, examination, investigation and evaluation items**

## 7.1 Schedule

|  | Obtaining  consent | Observational periods | | Treatment periods |
| --- | --- | --- | --- | --- |
|  |  | V1 | V2 | V3/EOT |
| Week |  | Provisional registration | Before treatment/final registration | 4 weeks |
| Allowance |  | － | After provisional registration 2~4 weeks | ±7日 |
| Obtaining consent | ○ |  |  |  |
| Selection/exclusion criteria |  | ○ | 〇 |  |
| Subject background |  | ○ |  |  |
| Vital sign ^a^ |  |  | ○ | ○ |
| Subjective/objective symptoms findings |  |  | ○ | ○ |
| hematological tests |  |  | 〇 | ○ |
| Biochemical tests |  |  | 〇 | ○ |
| Provisional registration |  | ○ |  |  |
| Final registration/ Dosing start criteria |  |  | ◎ |  |
| Blood and stool for exploratory research samples* collection |  |  | ● | ● |
| Research drug prescription |  |  | ○ |  |
| Checking medication status |  |  |  | ○ |
| Investigation of concomitant medications |  | ○ | ○ | ○ |
| Investigation of adverse events |  |  |  |  |
| Patient Diary ^b^ |  |  |  |  |
| Patient Questionnaire^c^ |  |  | 〇 |  |
| questionnaire survey ^d^ |  |  | 〇 | 〇 |

*: Provide stool collection kits for V1 and V2.

a: Blood pressure Pulse

b: Provide patient diary (for observation period) to V1, check and collect from V2.

　 Provide patient diary (for therapeutic phase) to V2, check and collect to V3.

^c^： V2 Patient questionnaire will be administered on arrival at the hospital.

Patient questionnaires for the treatment period are provided to V2, and checked and collected by V3.

^d^: JPAC-QOL and constipation score (CSS) will be conducted at V2 and V3 visits.

